## Abstract

Infertility is a condition in which a woman has not been pregnant despite having had normal intercourse for 1 year. The number of unexplained infertile females is increasing because of late marriage customs, as well as environmental and lifestyle habits. In Korea, infertile females have been treated with Korean medicine (KM). However, these effects have not been objectively confirmed through clinical trials. Therefore, this study was conducted to demonstrate the effectiveness of herbal medicine treatment in infertile patients and to demonstrate the economic feasibility through economical evaluation with assisted reproductive technology.

This study is designed as a multicenter, single-arm clinical trial. All participants included will be from 3 Korean Medicine hospitals in Korea and will voluntarily sign an informed consent agreement. All recruited patients will conduct related surveys and tests, and be provided with treatment according to their menstrual cycle. Patients will take herbal medicines for 4 menstruation cycles and receive acupuncture and moxibustion treatment at 3 times (menstrual cycle day 3, 8, 14) during 4 menstruation cycles. They will also undergo an approximately 4 menstrual cycle treatment period, and 3 menstrual cycle observation period. If pregnant during the study, participants will take the herbal medicine for implantation for about 15 days. In this study, the primary outcome will be the clinical pregnancy rate, whereas the secondary outcome will include the implantation rate, ongoing pregnancy rate, and live birth rate.

Ultimately, this study will provide clinical data regarding the effectiveness and safety of KM treatment for females with unexplained infertility and important evidence for establishing standard KM treatments for unexplained infertility. Moreover, we will identify the most cost-effective way to treat unexplained infertility.

## Background

1

Infertility is a condition in which successful pregnancy has not occurred, despite normal intercourse over 12 months. Approximately, 9 to 18% of normal couples are infertile.^[1]^ In recent years, the number of elderly pregnancies has been increasing because of changing social trends. Moreover, infertile females are increasing due to stress, obesity, lack of exercise, and environmental pollution.^[2]^ The causes of female infertility are classified as ovulation factors, tubal and peritoneal factors, cervical factors, uterine factors, immunological factors, infection factors, and unexplained. Among these, unexplained infertility is estimated to occur in about 15% of patients.^[3,4]^

Since 2006, Korea has begun to support project medical expenses for infertility. Over the last 10 years, the supporting project for assisted reproductive technology (ART) has grown quantitatively, bringing about 32,000 in vitro fertilizations (IVF) and 30,000 intrauterine insemination (IUI) treatments annually. The total cost of the project is 85.7 billion won; however, the clinical pregnancy rate (CPR) is about 33.5% for IVF and 10% for IUI, which is not very different from 10 years ago.^[5,6]^

Korean medicine (KM) has long utilized acupuncture and herbal medicine treatment for the treatment of infertility.^[7]^ Specifically, KM is widely used as a primary or adjuvant therapy of infertility in Korea and to improve the success rate of ART.^[8–10]^ Many investigations of KM treatment for infertility have been conducted in Korea; however, most investigations of KM treatment were experimental studies, case reports, retrospective chart reviews, and questionnaire studies.^[11,12]^ Several projects recently conducted by local governments and the association of Korean medicine revealed that the results of KM to treat infertility were comparable with IUI.^[7,8,13,14]^ However, many of these studies did not employ standardized KM treatments for unexplained infertility. Moreover, very few studies have been conducted to collect evidence of KM treatment effects on unexplained infertility.^[15]^

Therefore, we have developed a protocol for presenting standard KM treatment of infertility, as well as confirming the effectiveness and safety of KM treatment of unexplained infertility and providing an economic evaluation when compared with ART.

## Methods/design

2

### Study aims

2.1

This clinical trial was conducted to confirm the clinical effectiveness and safety of KM treatment of unexplained infertility and to evaluate the cost-effectiveness relative to ART.

### Design/setting

2.2

This study was designed as a multicenter, single-arm prospective clinical trial. All participants included will be from 3 hospitals: Dongguk University Ilsan Korean Medicine Hospital, Kangdong Kyunghee Korean Medicine Hospital, and Wonkwang University Kwangju Korean Medicine Hospital. Participants will be recruited through advertisements on bulletin boards at each medical center. The total target sample size is 100 subjects. All participants will voluntarily sign an informed consent agreement. Moreover, all participants will be enrolled after screening via the inclusion/exclusion criteria. All recruited patients will perform related surveys and tests, and be provided with treatments (herbal medicine, acupuncture, moxibustion). They will undergo an approximately 4 menstrual cycle treatment period and a 3 menstrual cycle observation period. If pregnancy occurs during the study, we will offer the herbal medicine to participants for about 15 days. The costs spent (transportation, time, care) in the previous treatment of the participants of this clinical trial will be investigated and compared with the conversion cost of this trial.

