#### Exclusion criteria

2.4.2

(1)Unable to take herbal medicine, acupuncture, and moxibustion treatment during 4 menstruate cycle treatment periods;(2)Unable to participate in this clinical trial for 7 months;(3)Takes pregnancy-related medicine (e.g., hormones, other herbal medication, etc);(4)Planning to undergo artificial insemination or IVF;(5)A has irregularly menstruating occurring at intervals of less 21 days or more than 40 days(6)Male factor infertility;(7)Has ovulation factor infertility (polycystic ovary syndrome, thyroid disease, hyperprolactinoma, etc);(8)Has tubal or peritoneal or uterus factor infertility (endometriosis, pelvic inflammatory disease, uterine myoma, adenomyosis, etc);(9)Is diagnosed with dampness heat, kidney yin deficiency;(10)Has taken IVF than 4 times;(11)Has severe neuropsychological disease history;(12)Has a severe disease related to infertility (e.g., hypertension, diabetes, chronic/acute hepatitis, hyperlipidemia, cardiovascular disease, cancer, chronic/acute inflammatory disease, etc);(13)Has cancer history within 5 years;(14)Has a skin disease over an acupuncture/moxibustion point;(15)Has an allergy or hypersensitivity to treatment (herbal medicine, acupuncture, moxibustion);(16)Is planning to participate in another clinical trial within 3 months;(17)Does not have the ability to fill out forms.

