#### Economic evaluation

2.9.2

Economic evaluation will be conducted from a social perspective and all costs and results will be considered. The cost data per patient in this trial will be requested to submit medical institutions or card receipts for expenses incurred in the preclinical treatment. If patients cannot submit a receipt, we will conduct a survey of preclinical treatment cost. The cost of this trial will be calculated by converting this trial treatment schedule into a general treatment. Transportation costs and time costs will be used to existing values that patients had spent, and surveys will be conducted during the clinical trial period.

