In this study, we will set up standard prescriptions according to the menstrual cycle on the basis of various studies and the prescriptions applied for infertility in Korea's representative large Korean medicine clinics. The standardized comprehensive treatment that can be applied to infertile women will be set up by combining herbal medicine, acupuncture and moxibustion. Overall, the ultimate purpose of this trial is to evaluate the effectiveness and safety of KM treatment for unexplained infertility and to evaluate the cost-effectiveness relative to ART. A total of 100 patients will be classified by age group, after which they will receive herbal medicine treatment according to patient's menstrual cycle and the CPR, IR, OPR, and live birth rate will be evaluated. To confirm the safety of KM treatment, we will check for adverse events every visit. Moreover, to evaluate cost-effectiveness, we will compare the economical effectiveness with that of ART.^[33]^

It should be noted that this trial has limitations. Specifically, it is based on a single treatment group without a blind, randomized control group. Because people usually do not want to wait to conceive, it is not easy to set up a control group. Therefore, literature pertaining to ART will be collected and used to replace a control group to compare the effectiveness and cost-effectiveness. This study is funded by the Ministry of Health and Welfare and the Korea Health Industry Development Institute and the results will be grounds for national policy projects. Moreover, to compare the effectiveness and economics of ART, the recruitment was based on the percentage of assisted reproductive costs supported in the country in 2010.

Despite these limitations, this clinical trial is the first to obtain an objective basis for the effectiveness and safety of KM treatment. The cost comparison with ART is expected to confirm the economic feasibility of Korean medicine treatment, which will allow us to offer a new direction in the treatment of infertility treatment, which is biased toward ART in Korea. We also expect it to be used globally as an alternative to solve the unexplained infertility.

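### Participants' own earlier spending is not a valid ART comparator cost, and the article does not reconcile it with the ART literature that is to replace a control group

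*Protocol article*

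**What the plan says.** Section 2.1 of the protocol article gives as one aim "to evaluate the cost-effectiveness relative to ART", and the Discussion repeats it: "to evaluate cost-effectiveness, we will compare the economical effectiveness with that of ART".

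The cost sources are described in two places.

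- Section 2.2 (Design/setting) states the cost contrast. Transport, time and care costs "in the previous treatment of the participants of this clinical trial will be investigated and compared with the conversion cost of this trial".
- Section 2.9.2 (Economic evaluation) says how the earlier costs are obtained. Patients are "requested to submit medical institutions or card receipts for expenses incurred in the preclinical treatment", with a survey where no receipt exists. For the Korean medicine side, "The cost of this trial will be calculated by converting this trial treatment schedule into a general treatment". It adds: "Transportation costs and time costs will be used to existing values that patients had spent", with further surveys during the trial.

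The Discussion (section 3) brings in another source. Because there is no control arm, published ART literature is to take its place for the comparison of both effectiveness and cost-effectiveness.

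Two eligibility rules bear on this. Section 2.4.1 requires a certificate of unexplained infertility. Section 2.4.2 restricts earlier IVF with the incomplete phrase "Has taken IVF than 4 times". No criterion requires any earlier ART.

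**The concern.** A cost-effectiveness comparison with ART needs an ART cost and an ART effect that belong to the same women, over the same unit of treatment. The only comparator cost that sections 2.2 and 2.9.2 name is what the enrolled women spent before the trial. These women are infertile at entry, so women whose ART resolved their infertility are largely absent from the cost sample. A success rate taken from the literature does include such women.

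The earlier spending also need not be ART spending. One participant may have paid for several IVF cycles, another for IUI, another for care that is not ART, and another for nothing.

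The article says the results are to inform national policy on infertility treatment. A ratio whose cost and effect come from different populations would have no clear meaning for that purpose.

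**Working it through.** **No figure to reproduce.** The article states no cost per patient and no cost-effectiveness ratio. The check sets the sections side by side and then illustrates the selection.

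**Step 1. Sources of each component**

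| Component | Source | Who it describes |
|---|---|---|
| Korean medicine cost | Trial schedule converted to ordinary care (2.9.2) | Trial participants |
| Cost it is compared with | Participants' previous treatment, by receipt or survey (2.2, 2.9.2) | Women infertile at entry, with or without earlier ART |
| ART effect | Literature (3) | Published ART users |
| ART cost-effectiveness | Literature (3) | Published ART users |

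Rows 2 and 4 both bear on the ART side of the economic comparison. No section says which is used or how they combine.

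**Step 2. Illustration of selection on non-success.** The inputs are the clinical pregnancy rates in the Background: p = 0.335 for IVF and p = 0.10 for IUI. The following are assumptions and are not in the article: p applies per cycle and is constant, cycles are independent, a woman stops at success, and she has at most K cycles, with K = 1 to 4.

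- Cumulative success by K cycles: 1 − (1 − p)^K
- Mean cycles per woman, unselected cohort: [1 − (1 − p)^K] / p
- Cycles used by a woman still not pregnant: K
- Ratio: K·p / [1 − (1 − p)^K]

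For IVF with K = 4: the cumulative rate is 1 − 0.665^4 = 0.804, mean cycles are 0.804/0.335 = 2.40, and the ratio is 4/2.40 = 1.67.

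| K | IVF cumulative rate | IVF mean cycles, unselected | IVF ratio | IUI ratio |
|---|---|---|---|---|
| 1 | 0.335 | 1.00 | 1.00 | 1.00 |
| 2 | 0.558 | 1.67 | 1.20 | 1.05 |
| 3 | 0.706 | 2.11 | 1.42 | 1.11 |
| 4 | 0.804 | 2.40 | 1.67 | 1.16 |

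**Step 3. What a matched source gives.** With cost and effect from the same unselected cohort, cycles per clinical pregnancy are 1/p whatever K is: 1/0.335 = 2.99 for IVF and 1/0.10 = 10.0 for IUI.

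**Step 4. What a mismatched pairing could give for IVF.**

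- Total cycles of women still not pregnant divided by the cumulative rate, K / [1 − (1 − p)^K]: 2.99, 3.59, 4.25 and 4.97 for K = 1 to 4.
- The same total divided by the per-cycle rate, K/p: 2.99, 5.97, 8.96 and 11.94.

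The larger multiples arise only in the second pairing, which the article does not specify.

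**Step 5. The bias can reverse.** Suppose a share s of participants had 2 earlier IVF cycles each and the rest had none. Averaging over all participants and dividing by the per-cycle rate gives 2s/0.335. For s = 0, 25, 50, 75 and 100% this is 0, 1.49, 2.99, 4.48 and 5.97, against the matched 2.99. Below half, the ART cost is understated; above half, it is overstated.

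**The case against.** The strongest reply is that the Discussion already assigns the cost-effectiveness comparison to the ART literature. On that view the earlier spending is a separate cost description, or an input for transport and time under a societal perspective. The cost sections speak of previous treatment and never call it ART. This stands in part: reading the earlier spending as the ART-side cost is an inference from the stated aim. It does not remove the problem, because section 2.2 still commits to comparing that spending with the trial's converted cost, and neither 2.2 nor 2.9.2 mentions literature costs. If the spending is not ART spending, it is even less suitable as an ART comparator.

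A reader might go further and infer that the plan adds up spending over failed attempts and credits ART with a single attempt's success, so that ART cost is inflated severalfold in favour of Korean medicine. The document does not support this. No section sums costs over attempts or divides them by 33.5%, and the Background does not state that 33.5% is a per-cycle rate. If costs were handled per procedure, the effect of attempt count would disappear.

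Three smaller points also stand. Secondary infertility is not excluded, so some earlier treatment may have succeeded. Look-back period and costing unit are details that an article commonly leaves to the full protocol, and their absence is not held against it here. The economic evaluation is listed as an additional analysis, so the primary outcome, the clinical pregnancy rate, is unaffected.

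**Conclusion.** The point holds as a conflict between stated sources and as an unsuitable comparator cost. Run as sections 2.2 and 2.9.2 describe, the cost contrast uses spending by women who are infertile at entry, with no requirement that any of it was for ART. The ART effect, and by the Discussion also the cost-effectiveness comparison, comes from literature on other women. This is a stated choice and not merely an omitted detail.

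Neither the direction nor the size of the bias can be read from the document. The ratios of 1.00 to 1.67 for IVF and 1.00 to 1.16 for IUI rest on a constant per-cycle success rate, independent cycles, stopping at success and at most 1 to 4 cycles. They show how selection on non-success works and are not estimates for this trial. If few participants had earlier ART, the error would run the other way. The matter is important because cost-effectiveness against ART is a stated aim with an intended policy use.

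**What to change.** 1. Reconcile sections 2.2, 2.9.2 and the Discussion, so that one source of ART cost is named for the cost-effectiveness comparison.
2. Take ART cost and ART effect from the same source and on the same unit: either cost and pregnancy rate per procedure, or cumulative cost and cumulative rate over a stated horizon.
3. Report participants' earlier spending descriptively, outside the ratio. Say how much of it was for ART and how many participants had none.

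This needs rewording and the extraction of unit costs during an ART literature search that is already planned. It needs no new patient data. The downside is reliance on published unit costs. More participants or more complete receipts would not remove the selection.

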### Recruitment

2.3

Participants will be recruited through advertisements on bulletin boards at each medical center. The target sample size is 100 subjects. Screening will be performed before the trial to determine if patients fulfill the selection criteria. Final enrollment will be determined by survey of menstrual history, medical history, and questionnaire for infertility treatment.

### Eligibility criteria

2.4

#### Inclusion criteria

2.4.1

(1)Female over 20 and under 44 years of age;(2)Unexplained infertile female with a medical certification from a doctor of obstetrics-gynecology;(3)Has sexual intercourse more than twice a week.

#### Exclusion criteria

2.4.2

(1)Unable to take herbal medicine, acupuncture, and moxibustion treatment during 4 menstruate cycle treatment periods;(2)Unable to participate in this clinical trial for 7 months;(3)Takes pregnancy-related medicine (e.g., hormones, other herbal medication, etc);(4)Planning to undergo artificial insemination or IVF;(5)A has irregularly menstruating occurring at intervals of less 21 days or more than 40 days(6)Male factor infertility;(7)Has ovulation factor infertility (polycystic ovary syndrome, thyroid disease, hyperprolactinoma, etc);(8)Has tubal or peritoneal or uterus factor infertility (endometriosis, pelvic inflammatory disease, uterine myoma, adenomyosis, etc);(9)Is diagnosed with dampness heat, kidney yin deficiency;(10)Has taken IVF than 4 times;(11)Has severe neuropsychological disease history;(12)Has a severe disease related to infertility (e.g., hypertension, diabetes, chronic/acute hepatitis, hyperlipidemia, cardiovascular disease, cancer, chronic/acute inflammatory disease, etc);(13)Has cancer history within 5 years;(14)Has a skin disease over an acupuncture/moxibustion point;(15)Has an allergy or hypersensitivity to treatment (herbal medicine, acupuncture, moxibustion);(16)Is planning to participate in another clinical trial within 3 months;(17)Does not have the ability to fill out forms.

### Interventions

2.5

#### Herbal medicine

2.5.1

All participants will take the herbal medicine according to their menstrual cycle. The detailed herbs in the prescriptions are listed in Table 1. Onkyeong-tang is a popular prescription in Donguebogam that regulates the menstrual cycle and infertility.^[16]^ The prescription for ovulation and implantation has been made and used by authors from Dongguk University Ilsan Korean Medicine Hospital.^[17]^ This prescription was made by [name] on the basis of Yuklin-ju, Ontoyuklin-ju and Sutae-hwan. The 2 prescriptions have been used to investigate infertility over 3 years and 200 cases, and have therefore received consent for use as medication for clinical trials from the Society of Korean Medicine Obstetrics and Gynecology. Onkyeong-tang will be decocted 30 packs (120 cc/pack) and participants will be instructed to take the medicine orally twice daily between menstrual cycle day (MCD) 3 and 12. The prescription for ovulation and implantation will be decocted 30 packs (120 cc/pack). Participants will be instructed to take medicine orally twice daily between MCD 13 and 28 every menstrual cycle. All herbal medicines will be manufactured by Jaseng-medicinal decoctions outside of the hospital, where there are semi-good manufacture practice (GMP) facilities and GMP herbs are used.

**Table 1 T1:**
[figure not shown]
Contents of Onkyeong-tang and prescription for ovulation and implantation.

#### Acupuncture and moxibustion

2.5.2

All patients will receive acupuncture treatment on 14 acupoints, GV20, CV4, bilateral Ex-CA7, ST29, SP6, SP9, ST36, and PC6 using acupuncture needles 0.3 mm in diameter and 30 mm in length (Dong Bang, Gyeonggi-do, Korea). At GV20, practitioners will insert needles 5 mm into the scalp fascia. At other acupoints, needle insertion will be to a depth of 15 to 20 mm, depending on the region of the body into which the needles were inserted. These procedures will elicit de-qi sensation. We will use electro-acupuncture for maintain de-qi and infrared therapy to heat the lower abdomen. The electro stimulation will be administered for 20 minutes at low-continuous 2 Hz. Following elicitation of the de-qi sensation at CV4, we will apply moxibustion for 20 minutes. Acupuncture and moxibustion treatments will be performed at MCD 3, 8, and 14 during 4 menstruation cycles. If the patient becomes pregnant during treatment, these treatments will be stopped.

### Outcome measures

2.6

#### Primary outcome

2.6.1

The primary outcome of this study will be CPR. Clinical pregnancy was considered to be at least 1 gestational sac with fetal heart activity confirmed by ultrasound scan 5 to 6 weeks after pregnancy.^[18]^

#### Secondary outcome

2.6.2

The secondary outcome of this study will be implantation rate (IR), ongoing pregnancy rate (OPR), and live birth rate. IR is confirmed by at least 1 gestational sac after human chorionic gonadotropin positive.^[19]^ Ongoing pregnancies are defined as the presence of fetal cardiac activity beyond 12 weeks of gestation.^[20]^ OPR is defined as the number of ongoing pregnancies divided by the number of clinical pregnancies. Live birth is defined as the delivery of 1 or more living infant (have heart beats or have beats of umbilical cord or have definite movement of voluntary muscles).

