#### Sample size

2.6.3

We did not follow the general method to calculate sample size. The sample size of this study was determined by Ministry of Health and Welfare and Korean Health Industry Development Institute in accordance with study budget, period, and purpose. A total of 100 participants will be recruited, of which 5 will be 20 to 29 years old, 40 will be 30 to 35 years old, 40 will be 35 to 39 years old, and 15 will be 40 to 44 years old. The detail sample size is shown in Table 2, the number of participants by age is based on report of age of the National Supporting Program for Infertile Couples Analysis and Evaluation of supporting project for infertile couples in 2012.^[21]^ Age distribution of participants supported by IVF is shown in Table 3.

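### The ongoing pregnancy rate is defined per clinical pregnancy, so it measures continuation past 12 weeks rather than how often treated women reach an ongoing pregnancy

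*Protocol article*

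**What the plan says.** The design is uncontrolled: "This study was designed as a multicenter, single-arm prospective clinical trial" (section 2.2, Design/setting). The same section sets the size: "The total target sample size is 100 subjects".

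Three definitions bear on the point:

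- Primary outcome event (section 2.6.1): "Clinical pregnancy was considered to be at least 1 gestational sac with fetal heart activity confirmed by ultrasound scan 5 to 6 weeks after pregnancy".
- Ongoing pregnancy event (section 2.6.2): "Ongoing pregnancies are defined as the presence of fetal cardiac activity beyond 12 weeks of gestation".
- Ongoing pregnancy rate (section 2.6.2): "OPR is defined as the number of ongoing pregnancies divided by the number of clinical pregnancies".

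The Discussion then groups the rates as what the study will assess: "the CPR, IR, OPR, and live birth rate will be evaluated". It also says that published results on assisted reproductive technology (ART) will stand in for a control group when effectiveness and cost-effectiveness are compared. No section gives a second ongoing pregnancy rate per woman treated. OPR is the only one of the four rates for which the article states a denominator.

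**The concern.** The denominator of OPR is itself a result of treatment: it is the count of women who met the primary outcome. The women who never conceived drop out of the calculation, although they are the main evidence on whether the treatment works. What remains is the chance that a pregnancy with a heartbeat at the early scan still has one beyond 12 weeks. That describes early pregnancy loss, not effectiveness.

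The placing of the ratio adds to the problem. It carries the name of a success rate and is listed with the clinical pregnancy rate (CPR) and the live birth rate. The article quotes ART clinical pregnancy rates of 10% and 33.5%. A reader who sees an OPR near 80% or 90% in the same report could take it for a per-woman success rate, and the Discussion expects the results to inform national policy. In a single-arm study with no internal comparison, the denominator decides what the figure can be set against.

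**Working it through.** The article gives no expected OPR, no power and no calculated sample size (section 2.6.3: "We did not follow the general method to calculate sample size"), so there is no figure to reproduce. The check is what the definition returns under plausible counts.

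**Inputs**

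- Women enrolled, N = 100 (section 2.2).
- Clinical pregnancies, C = 10 or 34 per 100 women. These are the ART clinical pregnancy rates in the Background, 10% for insemination and 33.5% for IVF, the latter rounded up to a whole woman. The article does not say what CPR it expects in this trial, so they only set a range.
- Survival from clinical to ongoing pregnancy, 70% to 90%. This is an assumption, because the article gives no figure.
- Ongoing pregnancies, O = C × survival, rounded to whole women.

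**Formulas**

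- OPR as written = O / C
- Rate per woman enrolled = O / N
- Link between them: O / N = (C / N) × (O / C)

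**Results**

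| C | Assumed survival | O | OPR as written, O/C | Per woman, O/100 |
|---|---|---|---|---|
| 10 | 70% | 7 | 70% | 7% |
| 10 | 80% | 8 | 80% | 8% |
| 10 | 90% | 9 | 90% | 9% |
| 34 | 70% | 24 | 71% | 24% |
| 34 | 80% | 27 | 79% | 27% |
| 34 | 90% | 31 | 91% | 31% |

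Two comparisons show the problem.

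1. *Insensitive to conception.* At 80% assumed survival, OPR is 80% (8/10) or 79% (27/34). The number of women who reach an ongoing pregnancy differs by a factor of 27/8 = 3.4.
2. *Order reversed.* 9/10 gives an OPR of 90% with 9 women per 100, while 27/34 gives 79% with 27 women per 100. The result with one third as many ongoing pregnancies has the higher OPR.

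The link formula also shows the limit of the point. If CPR is per woman enrolled, the per-woman rate is CPR × OPR: 0.10 × 0.80 = 0.08, and 0.34 × 0.794 = 0.27.

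**The case against.** The best defence is that no information is lost. Section 2.8 promises frequencies with percentages for categorical outcomes, so the ongoing pregnancy count will be visible and anyone can divide it by the number enrolled. With a single arm, conditioning on a post-treatment event biases no randomised comparison. OPR is one of three secondary outcomes and carries no decision rule. A continuation ratio is also a legitimate descriptive measure of early loss. All of this stands, and it limits the point to what the outcome measures and what it is called. It does not remove the point, because readers should not have to rebuild a named secondary outcome from its counts.

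Four stronger readings are tempting, and the document does not support them.

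- *The implantation rate has the same fault.* A reader might infer this from "IR is confirmed by at least 1 gestational sac after human chorionic gonadotropin positive". That sentence says how and when the event is confirmed and gives no denominator.
- *CPR and live birth rate need redefining too.* Their denominators are not stated, which a condensed article may leave to the full protocol. Nothing shows that they are not already per woman enrolled.
- *The per-woman rate would be estimated more precisely.* Its exact 95% interval is narrower in percentage points: 3.5% to 15.2% for 8/100, against 44.4% to 97.5% for 8/10. But these are different quantities on different scales. Relative to the estimate, the per-woman interval is the wider one: 11.7/8 = 1.5, against 53.1/80 = 0.7. Precision is no argument for the change.
- *The comparison with ART will be distorted.* The article plans an effectiveness comparison with ART literature but does not say that OPR will be part of it, and the only ART pregnancy rates it quotes are CPRs. A misreading is possible; a planned wrong comparison is not shown.

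**Conclusion.** The point holds for OPR alone. The denominator is stated outright, so this is not a detail left to a fuller document. As written, OPR is the proportion of clinical pregnancies continuing beyond 12 weeks. Over the range used, it reads 70% to 91% while the share of enrolled women with an ongoing pregnancy runs from 7% to 31%, and the two can rank results in opposite order.

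These figures rest on the assumed 70% to 90% survival and on borrowed ART rates for conception. That the ratio leaves out women who did not conceive follows from the definition and needs neither assumption.

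A reader might go further and say that the outcome says nothing about how often treatment leads to an ongoing pregnancy. That is too strong, since its numerator divided by the number enrolled gives exactly that. The primary outcome is unaffected. The definition should be corrected, but it does not threaten the study's main result.

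**What to change.** In section 2.6.2, define OPR as the number of women with an ongoing pregnancy beyond 12 weeks divided by all enrolled women (full analysis set). Keep the present ratio as a separate, descriptive item under a name that says what it is, such as the proportion of clinical pregnancies continuing beyond 12 weeks, and show its numerator and denominator.

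The cost is one changed definition and one added descriptive line. No further data, visits or participants are needed, since both figures come from the same counts. The downside for the sponsor is that the reported OPR becomes much smaller: in the illustration with 8 ongoing among 10 clinical pregnancies, it falls from 80% to 8%.
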